#### Sample Size for Biomarkers

Biomarkers of cardiac function will be assessed in all participants in this study in combination with markers of inflammation. We will conduct exploratory analysis to explore the association between markers of inflammation (eg, IL-6) and other physical impairments experienced after ICU admission, such as pain. Pain scores will be assessed using the severity of pain question set of the BPI (where any response of > 0 indicates that at least mild pain in present).

Using data collected from a previous local study investigating the incidence of chronic pain in survivors of critical illness, the mean BPI score was 6.5 (SD, 2.63) at 3 months.^46^ No studies are available in the critical care field that have investigated inflammation and pain longitudinally across the recovery trajectory. As such, we used data describing the association between inflammatory markers and chronic back pain, which found that a two-point reduction in 10-point pain severity scale was associated with lower IL-6 levels.^47^ Given the heterogeneity of the critical care population, we opted for a conservative estimate of a one-point change in BPI score with an α of .05 and power of 80%.^48^ As such, a sample size of 69 patients (Fig 3) will be recruited for biomarker analysis, allowing for a 20% attrition rate (resulting from loss to follow-up and mortality). This sample size also will allow for detection differences in cardiac biomarkers such as N-terminal pro B-type natriuretic peptide seen in other studies with at least 80% power and a significance level of 0.05.^20^

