#### Population

Patients admitted to the ICU for sepsis, defined by internationally recognized Third International Consensus Definitions for Sepsis and Septic Shock definitions, will be considered for inclusion. Our study protocol is designed with a focus on patients receiving critical care during the convalescent phase of illness, and as such our findings will be most relevant to the population of survivors of intensive care.

After providing informed consent, patients will be recruited around the time of ICU discharge during which cardiac and inflammatory biomarkers and echocardiography were completed. Participants will be followed up 6 to 10 weeks after hospital discharge, when patient-reported functional outcome measures (PROMs) will be obtained, along with repeat cardiac and inflammatory biomarker analysis. A subgroup of patients will undergo echocardiography at baseline and CMR after discharge from hospital (Fig 2).

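### The 80% power claimed for 69 patients matches a one-sample calculation for a one-point BPI change and is not supported for the planned association between IL-6 and pain

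*Protocol article*

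**What the plan says.** All the inputs stand in the protocol article, under Sample Size for Biomarkers. The analysis is to "explore the association between markers of inflammation (eg, IL-6) and other physical impairments experienced after ICU admission, such as pain". From a previous local study, "the mean BPI score was 6.5 (SD, 2.63) at 3 months". From work on chronic back pain, "a two-point reduction in 10-point pain severity scale was associated with lower IL-6 levels". Citing the heterogeneity of the critical care population, the authors then write that "we opted for a conservative estimate of a one-point change in BPI score", "with an α of .05 and power of 80"%. The result is that "a sample size of 69 patients (Fig 3) will be recruited for biomarker analysis, allowing for a 20% attrition rate".

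On timing, the Population section says: "Participants will be followed up 6 to 10 weeks after hospital discharge, when patient-reported functional outcome measures (PROMs) will be obtained". The same sentence describes the cardiac and inflammatory biomarker analysis at follow-up as a repeat, and does not describe the PROMs that way. The Biomarkers section likewise gives two time points for the inflammatory markers.

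The text does not say what the one point is a contrast of: two time points, two groups of patients, or two levels of IL-6. It names neither a test nor a formula.

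**The concern.** A power statement has meaning only for a particular test of a particular contrast. Here the effect is worded as a change in BPI score, while the analysis is an association between IL-6 and pain. A calculation for a mean change has no IL-6 term. It needs two BPI scores per patient, or a fixed reference score, and the text describes neither.

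The relationship between inflammation and chronic pain is one of the study's six aims, and 69 is its total recruitment target. If the 80% is taken at face value, a null IL-6 and pain result could be reported as coming from an adequately powered analysis. Calling one point conservative, against a literature effect of two points, also suggests a margin of safety that may not exist.

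**Working it through.** **Inputs.** SD 2.63, effect 1 point, α 0.05, power 80% and attrition 20%, all from Sample Size for Biomarkers. Two-sided testing is assumed, because the section does not state sidedness. z(0.975) + z(0.80) = 2.8016.

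**Reproducing 69.** One-sample or paired mean, normal approximation:

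n = (2.63 × 2.8016 / 1)² = 54.3, rounded up to 55; 55 / 0.8 = 68.75, rounded up to 69.

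This is an exact match. The one-sided version gives 43, then 54 after attrition, and does not match. A two-group comparison at one point gives 109 per group by the normal approximation: 218 evaluable and 218 / 0.8 = 272.5, so 273 recruited. That does not match either. A two-group comparison at two points gives 28 per group, 56 in total and 70 recruited, which is close, but the section says it used one point.

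**Does that calculation describe the study?**
- It contains no IL-6.
- As a paired test it needs a second BPI score, which the text does not describe.
- As a paired test it also needs the SD of the change. The figure of 2.63 is the SD of a score at 3 months. The two are equal only if the within-patient correlation ρ is 0.5, since SD of change = 2.63 × √(2(1 − ρ)). Assuming ρ between 0.3 and 0.7, that SD runs from 3.11 to 2.04 and the evaluable number from 77 to 33.

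**What 55 evaluable patients give for an association.** The text leaves the IL-6 contrast open, so both natural readings are shown.

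*One point is the difference between patients with higher and lower IL-6, split into equal halves.* The standardised difference is 1 / 2.63 = 0.38. A two-sample t-test with 27.5 per group has 28% power (34% with all 69). The normal approximation gives 29% and 35%, and unequal splits of 2:1 and 3:1 with 55 patients lower it to 26% and 23%. The difference detectable with 80% power is 2.8016 × 2.63 × √(4/55) = 1.99 points, or 2.02 by the t-test. One point at 80% power needs 110 per group by the t-test.

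*One point is the BPI difference per 1 SD of IL-6.* If 2.63 is the total SD, r = 1 / 2.63 = 0.38. Power is then Φ(atanh(0.380) × √52 − 1.96) = Φ(0.400 × 7.211 − 1.96) = 82%, or 83% by simulation. If 2.63 is the residual SD, simulated power is 77%.

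**Detectable correlation.** With 55 patients, r = tanh(2.8016 / √52) = tanh(0.3885) = 0.37.

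**These are separate figures.** For roughly normal IL-6, a correlation of 0.37 implies a difference between halves of 0.37 × 2.63 × 1.596 = 1.55 points. The 2.0-point figure belongs to a different and less efficient analysis, the median split.

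**The case against.** The strongest reply is that 69 may be right for an association. The sample size for a regression slope of one BPI point per SD of IL-6, with 2.63 as the residual SD, is algebraically the same expression: 54.3, then 55, then 69. Power on that reading is close to 80%. This stands in part. It means the one-sample formula is an inference from the arithmetic, and the documents do not show that a paired test was used. It does not rescue the justification, because the section never expresses the effect per SD of IL-6, and it words it as a change in score.

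A reader might infer that the study simply fails to deliver its 80% power, with 28% as the true figure. The documents do not support that. The 28% requires IL-6 to be split into equal halves, and no section mentions splitting it.

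A reader might also infer that no within-patient BPI change can exist. That is likewise too strong. The text places PROMs at follow-up without saying only then, and the observation schedule in Figure 2 is not available here. A baseline BPI would still leave IL-6 out of the calculation and 2.63 as the wrong kind of SD.

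Finally, this is a pilot study, the pain work is labelled exploratory, and the imaging component's primary outcome is reduced LVEF. The same section also claims at least 80% power for differences in N-terminal pro B-type natriuretic peptide, so the pain calculation is not the only support offered for 69. These facts limit the consequence. They do not make the stated power figure apply to the stated analysis. Nor is this merely detail left to a fuller document: the article itself gives the effect, SD, power and sample size, and they do not fit the analysis it describes.

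**Conclusion.** The point holds as a mismatch between a stated power figure and the planned analysis. The size of 69 reproduces exactly as a one-sample or paired calculation, while the text plans an association with IL-6, describes the BPI at follow-up, and supplies a cross-sectional SD. The 80% power is therefore unsupported for that association. It is not shown to be false under every reading.

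With 55 evaluable patients, power is about 28% for a one-point difference between equal IL-6 halves and about 77% to 83% for one point per SD of IL-6. On the first reading the detectable difference is about 2.0 points, which is the literature effect the plan says it reduced, so the claimed conservatism disappears.

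These figures assume two-sided testing, 20% attrition as stated, an SD of 2.63 at 6 to 10 weeks (it was observed at 3 months) and approximate normality. Severity is moderate, because the analysis is exploratory and the sample size need not change.

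**What to change.** Keep 69. In Sample Size for Biomarkers, remove the description of a conservative one-point change and state the detectable effect for the planned analysis. For example: *With 69 patients recruited and about 55 evaluable, the study has 80% power (two-sided 0.05) to detect a correlation of about 0.37 between IL-6 and BPI severity at follow-up.*

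If IL-6 will instead be split at the median, say so and give a detectable difference of about 2.0 BPI points as its own figure. Do not present it as equivalent to a correlation of 0.37. If one point per SD of IL-6 was intended, state that, and say whether 2.63 is taken as the total or the residual SD.

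The cost is wording only: no extra patients, visits or measurements. The downside is that the stated detectable effect will look less favourable than the present text suggests.

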**Figure 3 fig3:**
[figure not shown]
Venn diagram showing structure of recruitment for the Characterisation of Cardiovascular Function in ICU Survivors of Sepsis study. Participants in the green area will undergo CMR, biomarker analysis, and patient-reported outcome measure analysis. Participants in the blue area will undergo patient-reported outcome measure and biomarker analysis only.

#### Trial Management and Timelines

This study will be conducted in line with the current Guidelines for Good Clinical Practice in Clinical Trials and Strengthening the Reporting of Observational Studies in Epidemiology statement guidelines.^49^ The Study Management Group includes individuals responsible for the day-to-day management of the study, including the chief investigator ([name]), representatives from the sponsor, and the principal investigators at the designated study sites ([name], [name]). This group will ensure adherence to the protocol and will take appropriate action to safeguard participants and the quality of the study itself. Decisions about continuation or termination of the study will be the responsibility of the sponsor.

## Discussion

CONDUCT-ICU is a prospective, observational, multisite imaging and biomarker cohort study of survivors of sepsis treated in the ICU aimed at characterization of cardiovascular function and functional impairments after admission. To our knowledge, the approach is novel in this population, allowing us to explore potential mechanisms that mediate adverse cardiovascular events associated with sepsis admission. CONDUCT-ICU will provide objective measurements of cardiac function, myocardial inflammation, edema, and scar, and these findings will be enhanced by the ability to explore associations with cardiac and inflammatory biomarkers in addition to PROMs.

Critical illnesses such as sepsis are associated with chronic immune activation and immunometabolic changes similar to those seen in chronic cardiovascular disease.^6^ These inflammatory and metabolic changes can result in atherosclerosis or cardiac remodelling that ultimately may predispose patients to hypertension, ischemic heart disease, or heart failure. Survivors of ICU admission represent a large population of patients at potential risk of chronic cardiovascular disease. CONDUCT-ICU will allow us to collate evidence prospectively to help support or refute proposed clinical mechanisms and to identify a group of patients who may be responsive to established therapeutics. Furthermore, we also will be able to explore other impairments such as chronic pain through the larger cohort of patients undergoing biomarker analysis.

We will recruit a deliberately heterogenous cohort of patients in terms of comorbidity, admission diagnosis, and hospital trajectory. In doing so, we will minimize selection bias and ensure that the findings will be generalizable. ICU admission has a great impact on patient quality of life, with nearly one-third of patients readmitted to the hospital within 90 days and almost one-half struggling to return to work within 1 year.^50^ As such, it is possible that we will lose a significant proportion of patients to follow-up. CONDUCT-ICU will inform attrition rates, sample sizes, and feasibility of outpatient investigations in this population. Incorporating the imaging component of CONDUCT-ICU into a wider cohort of patients undergoing biomarker analysis will allow us to minimize attrition from this arm of the study.

We recognize that this study has limitations. Although we are making efforts to exclude patients with established coronary artery disease or heart failure, we recognize that some patients may have unrecognized cardiovascular disease at the point of recruitment to the study, potentially confounding the results. Our methodology represents a pragmatic approach to recruiting in this patient cohort, balancing exclusion of confounders and avoidance of exposure to the burden of additional imaging or invasive angiography during what often is a prolonged and complicated stay. Exclusion of patients unable to give consent may result in selection bias, for example, through excluding patients because of delirium that has not yet resolved. Inclusion of these patients via other means such as proxy consent would present logistical and ethical challenges on follow-up, and as such we have excluded these patients from this initial feasibility study.

CONDUCT-ICU is a novel multimodal imaging and biomarker study that will give fundamental mechanistic insights into adverse cardiovascular outcomes after ICU admission with sepsis. It will provide key understanding into the role cardiovascular dysfunction may play in functional impairment after ICU care. Furthermore, it will provide key operational and pilot data for larger studies investigating mechanisms of functional impairments occurring after ICU care in sepsis and other critical illness.

